### Randomization

Once a participant is deemed eligible and has provided consent, they will be randomized to one of two treatment arms in a 1:1 ratio to receive the immediate or the deferred intervention with ER niacin. Prior to the initiation of the trial, a CTN staff member not directly associated with the implementation of the trial will use an SAS module (SAS Institute, Cary, North Carolina, United States) to generate sequential participant study identification numbers which will be loaded onto a webpage randomization system. The treatment groups will be: arm 1: ER niacin supplementation for 24 weeks followed by 24 weeks of ART alone, and arm 2: 24 weeks of ART alone followed by ER niacin supplementation for 24 weeks. When a participant is deemed eligible, the study coordinator signs onto the password-protected randomization webpage which issues the allocation. A transaction file records the study identification number, allocation and date and time of randomization.

Scheduled visits for arm 1 of this study will be screening (up to four weeks prior to treatment), week 0 (baseline), week 4, week 8, week 12, week 16, week 20, week 24, and week 48/final visit (or other if terminating early). Table 3 shows the arm 1 schedule of study events.

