#### T-cell activation in blood

Levels of T-cell activation will be assessed in blood samples on weeks 0, 24 and 48. This analysis will be performed using specific monoclonal antibodies (mAbs) as previously reported [51, 52]. Briefly, peripheral blood mononuclear cells (PBMCs) will be obtained by Ficoll-Hypaque density gradient centrifugation. The PBMCs will be either stained with the appropriate mAbs or stored in liquid nitrogen until used. T-cell subsets will be identified using a mAb cocktail specific for CD3, CD4, CD8, CD45RA, CCR7, CD27, CD38 and HLA-DR. One million PBMCs will be incubated in a 96-well polystyrene plate (Fisher Scientific, Ottawa, Ontario, Canada) in the dark at 4°C for 30 minutes. The cells will be washed twice with phosphate buffer saline (Fisher Scientific, Ottawa, Ontario, Canada) containing 1% fetal calf serum (Sigma Aldrich, Oakville, Ontario, Canada), resuspended in 250 μL 2% paraformaldehyde (Sigma Aldrich, Oakville, Ontario, Canada) and stored at 4°C for up to 12 hours before flow cytometric analysis of cell surface expression. Unstained cells and fluorescence minus one mAbs will be used as controls in all experiments. Lymphocytes will be identified first according to their light-scattering properties and then analysed for expression of lymphocyte markers. CD4+ and CD8+ T-cells will be defined as CD3+ CD4+ CD8- T-cells and CD3+ CD4- CD8+ T-cells, respectively. The associated expressions of CD45RA, CCR7 and CD27 will be then used to obtain the percentages of cells distinctively identifying naïve (CD45RA+ CCR7+ CD27+), central memory (CD45RA- CCR7+ CD27+), pre-terminal effector memory (CD45RA- CCR7- CD27-) and terminal effector memory (CD45RA+ CCR7- CD27-) CD4+ and CD8+ T-cell subsets. The expression of the CD38 activation marker will be then determined for each CD4+ or CD8+ T-cell subset. FlowJo data analysis software (FlowJo, LLC, Ashland, Oregon, United States) will be used for data analysis.

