### Sample size and statistical analyses

Because this proof-of-concept study will explore a phenomenon with little *in vivo* data, a convenience sample of 20 participants was chosen without formal power calculations. The data that will be obtained should be sufficient to assist in such calculations for future large studies.

The primary comparison is the change in the percentage of CD3+ CD8+ HLA-DR+ T-cells between the period of ER niacin plus ART (from week 0 to week 24 of arm 1, and from week 24 to week 48 of arm 2) and the control periods of ART alone (from week 24 to 48 of arm 1, and from week 0 to 24 of arm 2). If the treatment effects in the two time periods look distinctly dissimilar, which may occur due to carryover effects of treatment, we will focus on the comparison between arms 1 and 2 at the end of 24 weeks.

In each time period, a between-groups t-test will be used to compare the change in the percentage of CD3+ CD8+ HLA-DR+ T-cells during the ER niacin plus ART treatment with the change in the percentage of CD3+ CD8+ HLA-DR+ T-cells in the ART treatment alone. If the results of these comparisons in the two treatment periods are similar, then within each treatment order, a paired t-test will be used to compare the change in the percentage of CD3+ CD8+ HLA-DR+ T-cells during the ER niacin plus ART period with the change in the percentage of CD8+ CD38+ T-cells during the ART-alone period and the results of these two comparisons will be combined to generate a pooled estimate of the treatment effect. The same analytic approach will be used for the secondary outcomes. The primary comparison would be based on 20 pairs of observations, with each subject receiving active ER niacin compared to the control time-points (ART alone without ER niacin) in different time-points. The ratio of the difference between the study groups to the standard deviation of the differences would have to be fairly large (0.625) to achieve a power of 80%. All statistical tests performed will be two-tailed with significance determined by reference to the 5% level, unless otherwise stated.

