The same analytic approach will be used for the secondary outcomes as for the primary outcome. The secondary outcomes are: the change in total CD4+ T-cell count, changes in Th17 cells and Treg cells in blood and gut mucosa samples (from substudy), changes in cytokines and in inflammatory markers such as IFN-α, IL-1, IL-6, IL-17, IP-10, D-dimers, hsCRP, sCD14 and LPS, the change in Trp plasma levels, changes in monocyte and dendritic cell immune activation, changes in cholesterol and triglycerides and changes in QoL, fatigue, depression and neurocognitive scores, using computerized and pencil and paper tests (from optional procedures).

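### The week 0-24 between-arm comparison is fixed as an unadjusted t-test of change; it is valid, but adjusting for the week-0 value already collected would usually be more precise

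*Protocol article*

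**What the plan says.** The analysis section of the Protocol article fixes the method for each period: "In each time period, a between-groups t-test will be used to compare the change in the percentage" of activated cells on niacin plus ART with the change on ART alone. It names no adjustment for the starting value, there or elsewhere.

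The week 0-24 result has two uses. It is one of the two period results compared before the within-order paired differences are pooled. If the periods look dissimilar, as carryover could cause, then "we will focus on the comparison between arms 1 and 2 at the end of 24 weeks".

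The method also extends beyond the primary endpoint: "The same analytic approach will be used for the secondary outcomes as for the primary outcome".

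On numbers, "a convenience sample of 20 participants was chosen without formal power calculations", and under Randomization "they will be randomized to one of two treatment arms in a 1:1 ratio", so about 10 per arm. On timing, the section T-cell activation in blood says: "Levels of T-cell activation will be assessed in blood samples on weeks 0, 24 and 48". Tables 3 and 4 mark week 0 for this measurement in both arms.

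**The concern.** The week 0-24 comparison is the one between-arm contrast that carryover cannot touch, because no participant has yet crossed over. The schedule has no washout: arm 1 stops niacin at week 24 and its control period starts at once. The Background says only that any decrease in activation may reverse after stopping. The fallback could therefore end up as the reported result, resting on about 10 participants per arm.

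A change score fixes the slope of the week-24 value on the week-0 value at 1. If the two visits have equal variances and correlate at rho below 1, the true slope is rho. Subtracting the whole baseline then removes too much and adds noise. Analysis of covariance estimates the slope. What is at stake is precision in a small comparison, for the primary marker and for each secondary outcome measured at week 0.

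**Working it through.** **Inputs from the Protocol article.** 20 participants, 1:1 allocation, two-sided 5% level, marker measured at weeks 0, 24 and 48. **Assumed, because the article gives no figure:** rho between week 0 and week 24, shown over a range, with the same standard deviation s at both visits.

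**The plan's own figure.** The analysis section says "The primary comparison would be based on 20 pairs of observations" and that the ratio of the difference to its standard deviation "would have to be fairly large (0.625) to achieve a power of 80" percent. With a paired normal approximation, (1.960 + 0.842)/√20 = 2.802/4.472 = 0.6265, and power at 0.625 is 79.8%, so the figure reproduces. (With a noncentral t on 19 degrees of freedom, power at 0.625 is 75.5% and the ratio needed is 0.660.) This figure concerns the pooled paired comparison. It does not describe the between-arm test at issue here.

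**The between-arm test as planned.** With 10 per arm and a t-test on 18 degrees of freedom, 80% power needs a difference of about 1.32 standard deviations of the change. The standard deviation of the change is s√[2(1 − rho)], which equals s at rho 0.5.

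**Variances, 10 per arm.**
- Change score: 2(1 − rho)s² × 2/10 = 4(1 − rho)s²/10.
- Adjusted for week 0, large-sample: 2(1 − rho²)s²/10.
- Large-sample ratio, adjusted to change: (1 + rho)/2.
- Cost of estimating the slope at N = 20: multiply by 1 + 1/(N − 4) = 1 + 1/16 = 1.0625.

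The last column of the table comes from simulation (40,000 trials per rho, t critical values on 17 and 18 degrees of freedom). The effect is set so that the change-score test has 80% power.

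| rho | (1 + rho)/2 | × 1.0625 | Power of adjusted test where the change test has 80% |
|---|---|---|---|
| 0.3 | 0.65 | 0.69 | 92% |
| 0.5 | 0.75 | 0.80 | 88% |
| 0.7 | 0.85 | 0.90 | 84% |
| 0.8 | 0.90 | 0.96 | 81.5% |
| 0.88 | 0.94 | 1.00 | 80% |
| 0.95 | 0.975 | 1.04 | 79% |

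Break-even: (1 + rho)/2 × 1.0625 = 1 gives rho = 2/1.0625 − 1 = 0.88.

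At a fixed effect of 1.0 s, an arbitrary size chosen for illustration, simulated power goes from 43% to 58% at rho 0.3, 56% to 66% at 0.5, and 78% to 81% at 0.7. It is 92% for both at 0.8. Type I error was about 5% for both methods.

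**CD4 count.** Entry requires a count of 350 cells/μL or less within four weeks before week 0. This narrows the week-0 spread relative to week 24, so the equal-variance formula no longer applies. As an illustration, assume participants are the lowest 30% on a screening value that correlates 0.9 with week 0. The simulated variance ratio is then about 0.87 at rho 0.3 (rho before selection), rising to about 1.0 at rho 0.7 to 0.8.

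**The case against.** The strongest reply is that nothing in the plan is wrong. Randomization makes the t-test of change unbiased and valid, and its type I error is nominal. The trial is a 20-person pilot, and the planned primary estimate is the pooled paired one, which this point leaves alone. The participants are virologically suppressed on stable ART, so rho could be high and the gain small. All of that stands. It limits the point to efficiency in the pooling check and the conditional fallback.

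A reader might infer more than the documents support:

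- *That the planned test is biased by regression to the mean.* A chance baseline imbalance shifts the change-score estimate in a given trial, but over randomizations there is no bias.
- *That CD4 count suffers most because participants are selected on a low count.* Selection acts on both arms alike, so it does not bias the contrast. By narrowing the week-0 spread it tends to reduce the gain from adjusting.
- *That the adjusted week-24 estimate is as precise as the pooled crossover estimate.* The large-sample variances do agree at rho 0.5 (0.15 s² each), but only with equal correlations across visits and no reversal of niacin's effect after stopping. The article allows for reversal. At N = 20 the adjusted figure is also nearer 0.15 × 1.0625 = 0.159 s².
- *That adjustment is free.* At this sample size it costs a degree of freedom and about 6% in variance, which cancels the gain at high rho.

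A further fair objection is that changing the method in period 1 alone would spoil the comparison of the two periods' effects. The fix has to deal with that.

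**Conclusion.** The point holds as an efficiency recommendation. The article commits to an unadjusted t-test of change for the week 0-24 comparison, although the covariate that would usually sharpen it is already collected in both arms. With equal variances and 10 per arm, adjustment cuts the variance by about 31%, 20%, 10% and 4% at rho 0.3, 0.5, 0.7 and 0.8. It gains nothing from about 0.88 upward and loses about 4% at 0.95. The possible gain is much larger than the possible loss over the range of rho shown. The size in this trial is unknown because the article gives no rho, and for CD4 count it may be small or nil. The planned test remains valid, and the pooled paired analysis is unaffected.

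**What to change.** State that, for weeks 0 to 24, the between-arm treatment effect is estimated from a linear model of the week-24 value on arm and week-0 value. Apply it to the primary endpoint and to each secondary outcome with a week-0 measurement, and report the adjusted difference with its 95% confidence interval. Name this as the analysis to be reported if the fallback is invoked.

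Keep the unadjusted comparison of change in both periods for judging whether the two periods' effects are similar, so that like is compared with like. Do not use the week-24 value as the baseline covariate in period 2: in arm 1 it has already been affected by niacin.

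No new visit, sample or participant is needed. The cost is analysis wording, one degree of freedom, and a small-sample variance penalty of about 6% that outweighs the benefit only when rho exceeds about 0.88 under equal variances (lower where the week-0 range is restricted, as for CD4 count). The model also yields an estimate of the residual variance, which would help the power calculations that this pilot is meant to inform.

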### Study outcome measures

The primary objective of this study will be to assess the impact of ER niacin supplementation in combination with ART compared to ART alone on T-cell immune activation as defined by changes in the percentage of CD8+ CD38+ HLA-DR+ T-cells.

The secondary objectives of this study will be to: 1) assess the change in total CD4+ T-cell count after ER niacin administration; 2) explore the effect of ER niacin on Th17 and Treg cell frequencies in blood; 3) explore the effect of ER niacin on cytokines and inflammatory markers such as interferon-alpha (IFN-α), IL-1, IL-6 and IL-17, interferon gamma-induced protein 10 (IP-10), D-dimers, highly-sensitive C-reactive protein (hsCRP) and LPS; 4) assess the influence of ER niacin on Trp plasma levels; 5) assess changes in cholesterol and triglyceride levels; 6) evaluate the impact of ER niacin on QoL, fatigue, depression and neurocognitive scores; and 7) explore ER niacin tolerance.

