### Efficacy variables

#### T-cell activation assessments

The primary endpoint of this study will be changes in the percentage of CD8+ CD38+ HLA-DR+ T-cells which will be used as a marker for the change in the level of T-cell activation. Enumeration of the CD38 activation marker on total CD4+ and CD8+ T-cells, as well as on naïve, memory and effector cell subsets, will be performed by eight-color flow cytometry. This will allow for the precise identification of which cell subpopulation(s) is or are more likely to downregulate CD38 expression following ER niacin administration.

The absolute numbers of activated T-cell subsets will be computed using: 1) the white blood cell (WBC) count; 2) the percentage of lymphocytes; 3) the percentage of CD4+ and CD8+ T-cells; and 4) the percentage of each CD4+ or CD8+ T-cell subset (naïve, central memory, pre-terminal effector memory or terminal effector memory).

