## Discussion

ART therapy has significantly decreased HIV-associated morbidity and mortality over the last 15 years. Despite the substantial benefits of ART, immune reconstitution may not be complete for approximately 30% of patients who achieve virologic control [1, 2]. These patients remain at an elevated risk for clinical progression to both AIDS and non-AIDS events [1, 3–5].

We have designed a proof-of-concept study to assess supplementation with Niaspan FCT (an ER form of niacin) in combination with ART, compared to ART alone, on T-cell immune activation as defined by changes in the percentage of CD3+ CD8+ HLA-DR+ T-cells. A reduction in immune activation may improve CD4 recovery in HIV-infected individuals with suboptimal immune responses despite sustained virologic suppression. Our study also includes a neurocognition substudy that examines the effect of niacin on QoL, fatigue and depression.

It has been previously reported that a 10-fold difference exists between uninfected healthy controls and treated aviremic HIV-infected participants in the level of activated CD3+ CD8+ HLA-DR+ T-cells [52, 56]. It is expected that a 50% reduction in activated CD3+ CD8+ HLA-DR+ T-cells will be observed following ER niacin treatment which should translate into a clinically significant increase in CD4+ T-cell count (>100 CD4+ T-cells/μL). This estimate is based on a mean increase of 100 CD4+ T-cells/μL for participants having a two-fold reduction or not in their CD8+ T-cell activation level after 48 weeks of ART [57]. Assessments of activated CD4+ CD38+ and CD8+ CD38+ cell subsets will allow, for the first time, a more precise definition of which cell subpopulation(s) may change with ER niacin. Measurements of circulating cytokines, inflammatory mediators and LPS will be used to determine whether ER niacin administration can reduce or suppress inflammatory mediators known to drive immune activation.

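### Every primary test is written on a marker other than the declared primary endpoint, and one clause of the paired test, read literally, compares two different markers across treatments

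*Protocol article*

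**What the plan says.** Under Study outcome measures the primary objective concerns "T-cell immune activation as defined by changes in the percentage of CD8+ CD38+ HLA-DR+ T-cells". The section on T-cell activation assessments is explicit: "The primary endpoint of this study will be changes in the percentage of CD8+ CD38+ HLA-DR+ T-cells". The Abstract, the end of the Background, the Study design and the Research hypothesis use the same double-positive phenotype. The Background also describes enhanced T-cell activation as CD38 and HLA-DR expressed together on CD8+ T-cells.

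The section on sample size and statistical analyses uses another label: "The primary comparison is the change in the percentage of CD3+ CD8+ HLA-DR+ T-cells between the period of ER niacin plus ART" and the control periods. The between-groups t-test in each period uses that label on both sides. If the two periods give similar results, "a paired t-test will be used to compare the change in the percentage of CD3+ CD8+ HLA-DR+ T-cells during the ER niacin plus ART period", and the comparator is introduced by the words "during the ER niacin plus ART period with the change in the percentage of CD8+ CD38+ T-cells during the ART-alone period". The paired results from the two treatment orders are then combined into one estimate of the treatment effect. If the periods look dissimilar, the focus moves to the comparison of arms at 24 weeks.

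The Discussion restates the aim "as defined by changes in the percentage of CD3+ CD8+ HLA-DR+ T-cells". It uses the same HLA-DR+ label for a cited 10-fold difference between healthy controls and treated patients, and for an expected 50% reduction on niacin.

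**The concern.** There are two separate problems.

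First, the declared endpoint and the stated primary tests concern different cell populations. The double-positive cells are a subset of the HLA-DR+ cells, so the two percentages need not move together. The endpoint section itself expects that CD38 may be downregulated on niacin. If CD38 fell on HLA-DR+ cells while HLA-DR did not change, the declared endpoint would fall and the HLA-DR+ percentage would not. The pilot is also meant to inform power calculations for later studies, so its mean and SD must belong to a defined variable.

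Second, the paired test as written takes one marker from the niacin period and another from the ART-alone period. Any difference in how these markers change over 24 weeks would be counted as a niacin effect.

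**Working it through.** **Step 1. Marker by place in the protocol article.**

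- Objective, hypothesis and endpoint sections: CD8+ CD38+ HLA-DR+.
- Primary comparison: CD3+ CD8+ HLA-DR+ in both periods.
- Between-groups t-test in each period: CD3+ CD8+ HLA-DR+ on both sides.
- Paired t-test (only if the periods look similar): CD3+ CD8+ HLA-DR+ on niacin, CD8+ CD38+ on ART alone.
- Week-24 fallback: no marker of its own. It takes over CD3+ CD8+ HLA-DR+ from the period-1 test.

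No test in the list uses the declared endpoint, and no sentence reconciles the labels.

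**Step 2. Does pooling the two orders cancel the marker difference?** Let a1 and a2 be the mean changes in HLA-DR+ without niacin in periods 1 and 2, b1 and b2 the same for CD38+, and τ the niacin effect on HLA-DR+. Assume no carryover and equal weight for the two orders (allocation is 1:1).

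One marker on both sides:
- Arm 1: (a1 + τ) − a2
- Arm 2: (a2 + τ) − a1
- Average: τ

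The clause as written:
- Arm 1: (a1 + τ) − b2
- Arm 2: (a2 + τ) − b1
- Average: τ + (a1 + a2)/2 − (b1 + b2)/2

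The crossover removes a period effect within one marker. It does not remove a marker difference that always goes with treatment. With τ = 0 the contrast is zero only if the two markers have the same average change on ART, which the article does not state.

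**Step 3. The plan's own figure.** The article says that 20 pairs need a standardised difference of 0.625 for 80% power at two-sided 5%. The normal approximation gives (1.960 + 0.842)/√20 = 2.802/4.472 = 0.626, so the figure reproduces. (The exact paired t-test with 19 df has 75.5% power at 0.625 and needs 0.660 for 80%; this is a side remark.) The figure is in units of the SD of the differences, so naming one marker throughout does not change it.

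**Step 4. Possible size of the error under the literal clause.** The article gives no mean change or SD for either marker, so the inputs here are assumptions. Let δ be the difference in average drift between the markers, in SDs of the paired difference, with τ = 0. Treat the analysis as one paired t-test on 20 pairs, two-sided 5%, 19 df, noncentrality δ√20.

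- δ = 0: noncentrality 0, rejection 5.0%
- δ = 0.10: 0.10 × 4.472 = 0.447, rejection 7.1%
- δ = 0.25: 0.25 × 4.472 = 1.118, rejection 18.6%
- δ = 0.50: 0.50 × 4.472 = 2.236, rejection 56.5%

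With 18 df, closer to pooling two within-order tests, the last two values are 18.5% and 56.2%. The calculation ignores the preliminary check that the periods look similar.

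**The case against.** The strongest reply is that the cross-marker clause is a slip. The sentence that defines the primary comparison uses one marker for niacin and control periods, the between-groups test does the same, and the sentence on 20 pairs sets each participant's niacin period against that participant's own control period, which presumes one variable. The paired test is also conditional, and the week-24 fallback has no cross-marker problem. Participants have been on stable ART for more than 12 months with suppressed virus, so the article gives no reason to expect a large difference in drift. The trial is a proof-of-concept study with a convenience sample.

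Most of this stands, and it limits the point. A reader might infer that the pooled estimate will not be a treatment effect. That holds only if the clause is carried out against the rest of its own section. A reader might also infer three rival primary endpoints, but CD8+ CD38+ is never named as an endpoint: it stands once in the analysis section and, in the Discussion, among additional subset assessments. Nor can one say that the tests depart from the registered endpoint, because the article gives only the registration number and date. The section on T-cell activation in blood ends with "The expression of the CD38 activation marker will be then determined for each CD4+ or CD8+ T-cell subset", but its antibody panel includes both CD38 and HLA-DR. That is condensed laboratory detail, not a contradiction.

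The reply does not remove the main mismatch. The HLA-DR+ label recurs throughout the analysis section and the Discussion, so it is not an isolated slip. With the clause corrected, the paired tests, the between-groups tests and the fallback would still be on a marker other than the declared one.

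**Conclusion.** The point holds as a contradiction between the declared primary endpoint and the stated primary analysis, on both the pooled path and the week-24 fallback. This needs no assumption; it follows from setting the sections side by side.

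The cross-marker comparison is a further defect of the operative text, probably unintended. Followed literally, it biases the pooled contrast by the difference between the two markers' average changes on ART. The size is unknown: about 5%, 7%, 19% or 56% false rejection at assumed differences of 0, 0.10, 0.25 or 0.50 SD, with the analysis treated as one 20-pair test. These rates show what could happen and do not predict what will. The 0.625 power statement is unaffected.

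**What to change.** - In the section on sample size and statistical analyses, use the endpoint from T-cell activation assessments (percentage of CD8+ T-cells co-expressing CD38 and HLA-DR) on both sides of the between-groups tests, the paired tests and the week-24 fallback.
- In the Discussion, align the sentence that states the study's aim. Leave the label on the cited 10-fold difference as it is, since a change could credit the cited sources with a marker they did not measure. Check in those sources which marker that figure and the expected 50% reduction refer to, and say so.
- If HLA-DR+ alone or CD38+ alone is reported, list each as a supportive outcome and compare it only with itself across periods.

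The cost is wording and a check of the cited sources. CD3, CD8, CD38 and HLA-DR are already in the antibody panel, so no new sample, visit or participant is needed. The trial is open-label, so the change should be made and dated before the activation results are examined by arm.

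### The detectable ratio of 0.625 for 80% power is a known-variance figure; the planned paired t-test on 20 pairs has about 75% power there and needs 0.66

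*Protocol article*

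**What the plan says.** All of this is in the Protocol article, section Sample size and statistical analyses. The section first says that 20 participants were taken as a convenience sample, with no formal power calculation. It then gives a sensitivity figure. The number of observations is fixed by "The primary comparison would be based on 20 pairs of observations". The effect measure is "The ratio of the difference between the study groups to the standard deviation of the differences", and this ratio "would have to be fairly large (0.625) to achieve a power of 80" per cent. On the significance level: "All statistical tests performed will be two-tailed with significance determined by reference to the 5% level".

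The tests are t-tests throughout. For the crossover analysis, "within each treatment order, a paired t-test will be used to compare the change" between the niacin and ART-alone periods, and "the results of these two comparisons will be combined to generate a pooled estimate of the treatment effect". Before that, "In each time period, a between-groups t-test will be used to compare the change" between arms. If the two periods disagree, "we will focus on the comparison between arms 1 and 2 at the end of 24 weeks". The article gives no detectable effect for that last comparison, no standard deviation, and no correlation between a participant's two period changes.

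**The concern.** The sentence fixes the number of pairs, the significance level, the power and the definition of the ratio, and the section names the test, so the figure can be checked without outside information. It matches the formula for a known standard deviation and not the test that is planned. With 20 pairs the standard deviation must be estimated from few observations, and the larger critical value of the t distribution has a visible cost.

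What is at stake is interpretation. A reader of a null result will use 0.625 to judge which effects the trial could have been expected to detect, and the article says that its data should help to size later studies. A sensitivity figure that is slightly too favourable makes a null result look a little more informative than it is.

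**Working it through.** **Inputs, all from the section named above:** n = 20 pairs; two-sided α = 0.05; power 80%; ratio d = mean difference / SD of the within-subject differences; paired t-test, combined over two treatment orders. The 1:1 allocation (section Randomization) gives 10 per arm.

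**1. Reproduce the stated figure.** Normal approximation:
- d = (z₀.₉₇₅ + z₀.₈₀)/√n = (1.960 + 0.842)/4.472 = 0.6265.
- Power at 0.625 = Φ(0.625 × 4.472 − 1.960) = Φ(0.835) = 79.8%.
- Pairs needed at 0.625 = (2.802/0.625)² = 20.1.

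So 0.625 is the two-sided normal value, slightly rounded. A one-sided 5% t-test on 19 degrees of freedom would have 85.3% power at 0.625, so that does not explain the figure.

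**2. Repeat with the planned test.** Under a true ratio d the t statistic is noncentral t with noncentrality d√n, here 0.625 × 4.472 = 2.795.

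| Analysis, 20 pairs | df | Critical value | Power at 0.625 | Ratio for 80% |
|---|---|---|---|---|
| Single paired t-test | 19 | 2.093 | 75.5% | 0.660 |
| Combined over two orders | 18 | 2.101 | 75.3% | 0.662 |

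The article does not say how the two orders are combined, so 18 degrees of freedom is an inference; the choice hardly matters. The shortfall against the 79.8% in step 1 is 79.8 − 75.5 = 4.3 points, and against the stated 80% it is 4.5 points. In pairs: at 0.625, 22 pairs give 79.8% and 23 give 81.7% (n − 1 degrees of freedom).

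**3. The week-24 comparison, 10 against 10.** For a two-sample t-test on 18 degrees of freedom the noncentrality is d′√(10/2), where d′ divides by the between-subject SD of the individual change. 80% power needs d′ = 1.32 (normal approximation: 2.802 × √(2/10) = 1.25).

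This denominator is not the one in the article's ratio. If both period changes have the same variance and correlation ρ, then SD of differences = SD of change × √(2(1 − ρ)). The article does not give ρ, so the values below are assumptions:

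| Assumed ρ | √(2(1 − ρ)) | Ratio for 80% on the article's scale | Multiple of 0.625 | Power at 0.625 on that scale |
|---|---|---|---|---|
| −0.5 | 1.732 | 0.76 | 1.2 | 63% |
| 0 | 1.414 | 0.94 | 1.5 | 46% |
| 0.25 | 1.225 | 1.08 | 1.7 | 37% |
| 0.5 | 1.000 | 1.32 | 2.1 | 26% |
| 0.75 | 0.707 | 1.87 | 3.0 | 15% |

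The two changes share the week-24 value with opposite signs, which pushes ρ downwards. With measurements of equal variance and equal correlation r at weeks 0, 24 and 48, each change has variance 2σ²(1 − r) and the covariance of the two changes is −σ²(1 − r), so ρ = −0.5.

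**The case against.** The strongest reply is that nothing depends on the figure. The sample is openly one of convenience, and neither its size nor any decision in the article is derived from 0.625. The sentence is a caution that the detectable effect is large, and 0.66 would carry the same caution. The figure also reproduces under a standard approximation, so it is not a slip of the pen. All of this stands, and it is why the point is minor. It does not make 0.625 the right value for the test that the section names.

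Two stronger readings are tempting and are not supported.

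- A reader might infer that the week-24 comparison needs twice the ratio, or has only 26% power at 0.625. Both put 0.625 and 1.32 side by side although they divide by different standard deviations. On the article's scale the multiple runs from 1.2 to 3.0 over the correlations shown, and is about two only near ρ = 0.5. What holds over that whole range is that the comparison falls short of 80% power at 0.625.
- A reader might infer a further, known loss from drop-out. The article gives no drop-out rate, and its sentence is conditional on 20 pairs. If one assumed 18 or 16 completers, power at 0.625 would be about 70% or 64%, but those counts are illustrations.

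Nor is it a defect in itself that a condensed article gives no detectable effect for the week-24 comparison.

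**Conclusion.** The stated figure is wrong for the named test, by a small amount. At 0.625 the two-sided 5% paired t-test on 20 pairs has about 75% power, and 80% needs 0.66. This rests on 20 complete pairs, on approximately normal within-subject differences, and on 18 or 19 degrees of freedom, which agree to two decimals of the ratio. The article does not claim 80% power for any effect that it expects, so the design does not fail a promise; only the published sensitivity figure needs correcting. Severity: minor.

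**What to change.** Restate the sentence so that 20 complete pairs give 80% power at a ratio of 0.66, or equivalently about 75% power at 0.625, by a two-sided 5% paired t-test.

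Optionally add that the week-24 comparison of 10 with 10 needs a difference of about 1.3 between-subject standard deviations of the individual change for 80% power, and say that this is not the standard deviation of the within-subject differences. Any conversion between the two scales should show an assumed range for the correlation, and any figure for fewer completers should be labelled as an assumption.

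The cost is one or two sentences. The sample size, the visits and the analysis stay as they are, and the stated sensitivity becomes slightly less favourable.
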